#### Quality of life questionnaire

2.5.20

The Minnesota Living with Heart Failure Questionnaire will be administered by the same trained investigator before and immediately after the 16-week cardiovascular rehabilitation protocol, utilizing the instrument validated for the Brazilian population [33]. This disease-specific questionnaire consists of 21 individual items designed to measure the patients' perceptions of the effects of heart failure on their physical, socioeconomic, and psychological lives.

Each question is scored on a 6-point Likert scale ranging from 0 (indicating no limitation) to 5 (indicating maximum limitation). The items are structurally divided into three distinct dimensions: a physical dimension, an emotional dimension, and a generalized dimension incorporating financial considerations and lifestyle constraints. The total cumulative score will range from 0 to 105 points, with a lower overall score reflecting a superior disease-specific quality of life.

The cutoff points used to categorize the participants' quality of life status will be defined as follows: scores up to 26 points indicate a good quality of life; scores from 26 to 45 points indicate a moderate quality of life; and scores higher than 45 points signify a poor quality of life [33,34].

#### Statistical analysis and machine learning plan

2.5.21

All primary and secondary clinical, functional, and biochemical outcome analyses will be conducted strictly based on the intention-to-treat principle. Accordingly, all randomized participants will be evaluated within their originally allocated treatment groups, regardless of compliance, session attendance, missing data, or subsequent protocol deviations. Continuous variables will be presented as mean plus or minus standard deviation for data with a normal distribution, or as median and interquartile range for non-normally distributed data.

Categorical variables will be expressed as absolute frequencies and percentages and will be compared utilizing the chi-square test. Continuous variables demonstrating normal distribution will be analyzed using analysis of covariance models, adjusted for age and sex as clinical baseline covariates. The essential prerequisites for the analysis of covariance models—including linearity, normality of distribution, and homogeneity of variance—will be strictly verified through visual inspection of histograms, normal probability plots, and residual scatter plots.

Continuous variables with non-normal distribution will undergo logarithmic transformation to correct distribution asymmetry. If normal distribution is not achieved following transformation, generalized linear models or robust statistical methods will be applied to guarantee appropriate adjustments for age and sex. All classical statistical analyses will be conducted utilizing the R Studio environment (version 1.12, R language version 4.2).

In addition to traditional frequentist statistical analyses, advanced machine learning and artificial intelligence techniques will be deployed to optimize data interpretation and discover predictive biomarkers of therapeutic response to the physical exercise interventions. To predict individual clinical responses to the cardiovascular rehabilitation protocol—specifically changes in N-terminal pro-brain natriuretic peptide, peak oxygen consumption, and quality of life scores—supervised learning algorithms will be implemented, including random forest, gradient boosting machines, and support vector machines. To mitigate the risk of model overfitting and ensure generalizability, these supervised algorithms will be evaluated using a k-fold cross-validation strategy.

Unsupervised learning methods, specifically k-means and hierarchical clustering algorithms, will be utilized to perform clinical phenotyping of patient subgroups based on multidimensional profiles incorporating baseline inflammatory, functional, and echocardiographic variables. Feature selection and model interpretability will be enhanced using least absolute shrinkage and selection operator regression alongside Shapley Additive exPlanations values to identify and rank the most relevant predictive clinical variables. Longitudinal data tracking dynamic trajectories of clinical response over time will be comprehensively analyzed using mixed-effects models and, where applicable, recurrent neural networks.

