**Fig. 1 fig1:**
[figure not shown]
Flow chart of study procedures.

Currently, cardiopulmonary rehabilitation (CR) holds a class I recommendation in guidelines from both the European Society of Cardiology and the American College of Cardiology [4,5]. Despite the established therapeutic role of physical training in HF populations, the heterogeneity of exercise interventions limits the consensus on the most effective prescription [6]. Furthermore, the limited global availability of structured rehabilitation programs negatively impacts patient outcomes and quality of life [7,8].

In part, the severe exercise intolerance observed in these patients reduces adherence and compromises the expected prognosis in conventional programs [9]. Traditional resistance training (CRT) typically requires moderate-to-high external loads (60–80% of 1-repetition maximum [1RM]) to induce muscular hypertrophy and strength gains. However, such intensities induce elevated central hemodynamic stress, which is often intolerable or contraindicated for individuals with advanced HF [10].

To overcome these limitations, resistance training combined with blood flow restriction (BFRRT) has emerged as a promising clinical strategy, having demonstrated safety and efficacy in other cardiovascular populations such as coronary artery disease and hypertension. By applying partial vascular occlusion to the working limbs, BFRRT allows the use of low external loads (20–30% 1RM) while mimicking the metabolic stress and hypertrophic stimuli of high-load training, thereby minimizing central cardiac overload [11,12]. However, evidence regarding BFRRT specifically in heart failure remains limited.

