### Sample size calculation

2.2

The sample size calculation was informed by the data reported by Tanaka et al. [13], who evaluated a BFR-based exercise protocol in patients with HF (New York Heart Association [NYHA] functional class I or II). In their trial, a post-training reduction in brain natriuretic peptide (BNP) of 73 ± 68 pg/mL was observed in the BFR group, compared to a reduction of 15 ± 70 pg/mL in the conventional CR control group [13].

Based on these values, a Cohen's *d* effect size of 0.83 was calculated. Assuming a 1:1 allocation ratio between the experimental arms, a minimum of 24 patients per group is required to achieve a statistical power of 80% with a two-tailed alpha level of 0.05. To account for an anticipated attrition rate of approximately 10%, the final sample size has been established at 26 patients per treatment arm, resulting in a total target recruitment of 52 participants. BNP data from Tanaka et al. were used as the closest available proxy because both biomarkers reflect cardiac wall stress and no directly comparable BFR exercise trial reporting NT-proBNP was available, although this trial will evaluate N-terminal pro-brain natriuretic peptide (NT-proBNP) as its primary biochemical outcome.

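### The intention-to-treat promise covers patients with missing data, but the ANCOVA named for the primary outcome has no way to include a patient without a week-16 NT-proBNP and does not list baseline NT-proBNP as a covariate

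*Protocol article*

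**What the plan says.** Section 2.5.21 applies one rule to the primary and secondary analyses: "outcome analyses will be conducted strictly based on the intention-to-treat principle". It spells this out: "all randomized participants will be evaluated within their originally allocated treatment groups, regardless of compliance, session attendance, missing data, or subsequent protocol deviations".

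The same section gives the model: "Continuous variables demonstrating normal distribution will be analyzed using analysis of covariance models, adjusted for age and sex as clinical baseline covariates". Skewed variables are log-transformed. If that fails, "generalized linear models or robust statistical methods will be applied to guarantee appropriate adjustments for age and sex".

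Later in the section, among the machine-learning methods, data on response trajectories over time "will be comprehensively analyzed using mixed-effects models". That sentence does not mention the primary outcome.

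Section 2.5.1 defines the primary outcome as the change in serum NT-proBNP from baseline to the end of the 16-week programme. Table 1 schedules the biochemical samples at T0, T1 (week 16) and T2 (month 12). Section 2.2 raises the sample from 24 to 26 per arm for an attrition of about 10%. Section 2.5.18 says in general terms that the biochemical markers, NT-proBNP among them, will serve as baseline covariates, but the model in Section 2.5.21 lists only age and sex.

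**The concern.** An article that says nothing about missing data would be no finding, because that detail can sit in a full protocol or analysis plan. This article does say something: missing data will not keep anyone out of the analysis. The model it names does not deliver that. T1 is the only post-baseline sample in the primary window, so a patient without it has no primary outcome value and drops out of an ANCOVA, a GLM or a robust regression unless a further method is added. The sample-size section points the same way, since it treats patients who are lost as contributing nothing.

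Two things are at stake. A comparison of patients with a week-16 sample could be reported as strict intention-to-treat. It could also be biased if the patients lost differ from those kept, and differ by arm. The article's own rationale makes this plausible. The Introduction says that "the severe exercise intolerance observed in these patients reduces adherence and compromises the expected prognosis in conventional programs", and one arm is a conventional programme at 60–80% of 1RM.

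**Working it through.** **1. The plan's own figures (Section 2.2).** The changes are −73 (SD 68) and −15 (SD 70) pg/mL of BNP, a difference of 58. The pooled SD is √((68² + 70²)/2) = 69.0, so d = 58/69.0 = 0.84; dividing by 70 gives the stated 0.83. A two-sided t-test at 0.05 with 80% power and d = 0.83 needs 23.8, so 24 per arm, as stated. Allowing for 10% loss, 24/0.9 = 26.7; the plan's 26 is close to that.

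**2. How many patients have no week-16 value.** At 10% loss, 52 × 0.9 = 46.8, so about 47 patients have a value and about 5 do not. Per arm, 26 × 0.9 = 23.4.

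**3. Power.** For d = 0.83, t-test power is 0.835 with 26 per arm, 0.804 with 24 and 0.793 with 23.4. Power is barely affected, so the issue is bias and labelling.

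**4. Bias when the lost patients' outcomes differ.** In one arm, the mean of observed patients minus the mean of all randomised patients is m × (mean of observed − mean of missing), where m is the fraction missing. The bias in the treatment contrast is the difference between arms. The article gives no loss or outcome shift by arm, so the following are assumptions.

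| Assumed loss | Shift 35 pg/mL (about 0.5 SD) | Shift 69 (about 1 SD) | Shift 138 (about 2 SD) |
|---|---|---|---|
| 10% in each arm, same shift in both | 0 | 0 | 0 |
| 10% in each arm, shift in one arm only | 3.5 (6% of 58) | 6.9 (12%) | 13.8 (24%) |
| 4/26 against 1/26, same shift in both | 4.0 (7%) | 8.0 (14%) | 15.9 (27%) |

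The last row is (4/26 − 1/26) × shift; for example, 3/26 × 69 = 8.0, and 8.0/58 = 14%. If these shifts are not explained by recorded data, this is missing-not-at-random loss, and no standard primary model removes it.

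**5. Bias when loss depends on baseline NT-proBNP.** Change correlates with baseline, so losing patients with particular baseline values in one arm moves that arm's mean change. In a simulation with 26 per arm, 4,000 trials per setting and a baseline-to-week-16 correlation of 0.5–0.7, loss was 13–24% and baseline-related in one arm, and 5–10% in the other.

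- Complete-case change score: bias of −0.038 to −0.100 baseline SD.
- The same data with baseline conditioned on: −0.007 to 0.002 baseline SD.

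The upper setting averages (24 + 10)/2 = 17% loss, above the planned 10%; the lower averages (13 + 5)/2 = 9%. These results are in baseline SD, whereas 0.83 is in SD of change, so they should not be read as a share of 0.83.

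**The case against.** The strongest reply is that nothing here is contradictory. ANCOVA and the promise are compatible once missing outcomes are imputed, and a condensed article may leave the imputation method to a document not shown. That stands against one tempting reading, namely that the primary result is a complete-case result. The article nowhere says that patients are excluded, so this can be inferred only from the named model. The reply does not remove the point: the article makes a positive statement about missing data and describes no analysis that carries it out.

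It can also be said that the mixed-effects sentence covers the primary outcome, since Section 2.5.1 calls that outcome a longitudinal change. That reading is possible. But the sentence sits with clustering and neural networks, while ANCOVA is what the section gives for continuous outcomes, so the assignment needs to be made explicit. Likewise, Section 2.5.18 hints at baseline NT-proBNP as a covariate without placing it in the model.

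A reader might further infer that dropout bias has been shown. It has not. The article reports no loss by arm. Poor adherence is not the same as a missing blood sample, and analysing patients whatever their attendance implies that those who stop training are still sampled. Patients unable to do resistance training are excluded at entry. With like loss in both arms the bias is zero.

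Finally, the simulated bias comes from not conditioning on baseline rather than from dropping patients as such. A patient with neither T1 nor T2 adds only a baseline value to a mixed model. This is correct, and it is why baseline-adjusted ANCOVA with multiple imputation is an acceptable alternative and why a sensitivity analysis is needed with either.

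**Conclusion.** The point holds in a limited form. The promise about missing data is not carried through to the model named for continuous outcomes, and that model does not list baseline NT-proBNP. As written, it would compare about 47 of 52 patients at the planned attrition.

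Bias arises only if loss is related to outcome and its pattern differs between arms. Under the assumed baseline-related loss it is about 0.04–0.10 baseline SD, and conditioning on baseline brings it to about 0. Under the assumed differential shifts in unobserved outcomes it is 6–27% of the planned 58 pg/mL, and neither proposed primary analysis would correct that part if the loss is missing-not-at-random. All these sizes rest on assumed loss patterns, since the article gives none. Power is not a concern. The article does not support the claims that the trial will exclude patients or that its result will be biased.

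**What to change.** State in Section 2.5.21 how a patient without a week-16 NT-proBNP enters the primary analysis. Either of these would do:

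- Assign the mixed-effects model already named there to the primary outcome: (log) NT-proBNP at T0, T1 and T2, with baseline as part of the response and a common baseline mean across arms, arm-by-visit terms, age and sex, and the T1 contrast as the primary test.
- Keep ANCOVA, add baseline NT-proBNP as a covariate, and use multiple imputation for missing week-16 values.

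With either, add one tipping-point analysis that shifts the missing T1 values in one arm by increasing amounts until the conclusion changes. Say also that the T1 sample is sought from patients who stop training, as the intention-to-treat rule already implies.

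The cost is wording and a little more analysis work, with no new patients or visits. The downside is that the primary analysis then rests on a missing-at-random assumption, which the tipping-point analysis examines but cannot verify.

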**ASSESSMENTS**						
Clinical (DXA, skinfolds, ABI)		X			X	X
Biochemical (BNP/NT-proBNP, microRNA)		X			X	X
Functional (CPET, 6MWT, sit-to-stand)		X			X	X
Imaging (transthoracic echocardiogram)		X			X	X
Strength (1RM test and retest)		X	X	X (adjustment)	X	X
Strength (isokinetic & handgrip)		X			X	X
Quality of life (Minnesota MLHFQ)		X			X	X
Clinical events & hospitalizations				X	X	X

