#### Primary outcome

2.5.1

The primary outcome of this trial will be the longitudinal change in serum N-terminal pro-brain natriuretic peptide (NT-proBNP) levels from baseline to the completion of the 16-week intervention. Serum NT-proBNP is a gold-standard, objectively measured biomarker reflecting myocardial wall stress and hemodynamic overload. Reductions in its concentration serve as a surrogate marker for positive cardiac reverse remodeling and are strongly correlated with reduced long-term cardiovascular mortality and hospitalization rates in individuals with heart failure.

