#### Biochemical tests blood

2.5.18

Blood samples will be collected via venipuncture after a strict 12-h overnight fast. All laboratory analyses will be executed at the central facility of the Catholic University of Brasília. Approximately 28 aliquots per participant will be prepared for immediate storage in liquid nitrogen at the facility, and 14 aliquots will be stored in ultra-low temperature freezers at minus 80 °C at the research center for future exploratory biomarker analyses.

The comprehensive laboratory panel will include whole blood cell count determined via an automated counter method. Metabolic and lipid profiles will comprise fasting plasma glucose, total cholesterol, high-density lipoprotein cholesterol, and triglycerides, all analyzed using the ADVIA Chemistry system (Siemens, Deerfield, Illinois). Low-density lipoprotein cholesterol will be calculated utilizing the Friedewald equation, or measured directly if triglyceride levels exceed 400 mg per deciliter.

To evaluate systemic inflammatory responses, organ function, and clinical safety markers, the panel will analyze high-sensitivity C-reactive protein and fibrinogen (Dade Behring; Siemens); creatinine, uric acid, calcium, gamma-glutamyl transferase, aspartate aminotransferase, and alanine aminotransferase (ADVIA Chemistry); glycated hemoglobin (Bio-Rad Laboratories, Hercules, California); and creatine phosphokinase to monitor skeletal muscle integrity.

Endocrine regulation and cardiac strain will be determined via thyroid-stimulating hormone, thyroxin, insulin, and C-peptide (Siemens). Crucially, N-terminal pro-brain natriuretic peptide (Dade Behring; Siemens) will be quantified as a primary biomarker of myocardial wall stress, and microalbuminuria (Dade Behring) will be assessed to track baseline microvascular renal function. These biochemical markers will be utilized to ensure patient safety compliance regarding renal and hepatic thresholds prior to exercise, and to serve as clinical baseline covariates.

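### The stated ANCOVA adjusts for age and sex but not for baseline NT-proBNP, which gives up precision and leaves the estimate open to chance baseline imbalance

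*Protocol article*

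**What the plan says.** Section 2.5.1 defines the primary outcome as the "longitudinal change in serum N-terminal pro-brain natriuretic peptide (NT-proBNP) levels from baseline to the completion of the 16-week intervention". The abstract also describes it as a change, and Section 2.2 sizes the trial on between-group differences in change.

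Section 2.5.21 gives the model. Normally distributed continuous variables are "analyzed using analysis of covariance models, adjusted for age and sex as clinical baseline covariates". Non-normal variables are log-transformed; if that fails, "generalized linear models or robust statistical methods will be applied to guarantee appropriate adjustments for age and sex". The covariate set is therefore written out twice, as age and sex each time. The section does not say whether the dependent variable is the change or the week-16 value.

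Baseline NT-proBNP will be available: the row "Biochemical (BNP/NT-proBNP, microRNA)" in Table 1 is marked at T0, T1 and T2. Section 2.5.18 lists NT-proBNP in a laboratory panel whose markers are "to serve as clinical baseline covariates", but it ties that role to no outcome and no model.

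**The concern.** In a randomised trial with a pre- and post-treatment measurement, the baseline value of the outcome is normally expected to be the most informative covariate. That is a general statistical expectation, not a figure in the article. Here the covariates are stated, and baseline is not among them.

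Two things are at stake. The first is precision: an unadjusted change score has a larger residual variance than the same comparison adjusted for baseline. The second is exposure to chance imbalance: the arm that happens to start higher is expected to fall further through regression to the mean, and an unadjusted change score credits that fall to treatment. The trial enrols HFrEF and HFpEF, NYHA II and III, with 26 per arm, and Section 2.5.3 describes permuted blocks without stratification. Nothing in the described design balances baseline NT-proBNP.

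The article is also inconsistent: Section 2.5.18 gives the biochemical markers a covariate role that Section 2.5.21 does not carry through.

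**Working it through.** **Inputs from Section 2.2.** "a post-training reduction in brain natriuretic peptide (BNP) of 73 ± 68 pg/mL was observed in the BFR group", against a reduction of 15 ± 70 pg/mL in controls; d = 0.83; 24 per group; 80% power; two-sided alpha 0.05; about 10% attrition; 26 per arm. The correlation r between baseline and week-16 values is not in the article. I assume 0.5 to 0.9, with equal variances at the two visits.

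**Reproducing the plan.** The difference is 73 − 15 = 58 pg/mL. The pooled SD is √((68² + 70²)/2) = 69.0, so d = 58/69.0 = 0.84; 58/70 gives the stated 0.83. A two-sample t calculation at d = 0.83 needs 23.8, rounded up to 24 per group, and 24 per group gives 80.4% power. The stated figure reproduces. With age and sex in the model but explaining nothing, power is 80.3%.

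**Effect of adding baseline.** Let σ be the SD at one visit.

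- Variance of the change: 2σ²(1 − r).
- Residual variance with baseline in the model: σ²(1 − r²).
- Ratio: (1 + r)/2, so the effective effect size becomes 0.83/√((1 + r)/2).
- If the week-16 value were modelled without baseline, the effective effect size would be 0.83 × √(2(1 − r)).

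Power is from the noncentral t at 24 per arm. Error degrees of freedom are 43 with baseline, age and sex, and 44 with age and sex alone. Age and sex are taken to explain nothing.

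| Assumed r | Variance ratio (1 + r)/2 | Power: change, age and sex | Power: baseline added | Contingency: week-16 value, age and sex |
|---|---|---|---|---|
| 0.5 | 0.75 | 80% | 90% | 80% |
| 0.7 | 0.85 | 80% | 86% | 59% |
| 0.8 | 0.90 | 80% | 84% | 43% |
| 0.9 | 0.95 | 80% | 82% | 24% |

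If 10% are lost from 26 per arm, 26 × 0.9 = 23.4 remain. Power on the change score is then 79%, and with baseline added it is 89%, 85%, 83% and 81% at the same correlations.

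**Effect of chance imbalance.** The one-standard-error baseline difference at 24 per arm is σ√(2/24) = 0.289σ. Given an imbalance, the unadjusted change contrast is shifted by (1 − r) times that imbalance. The planning SD of change implies σ = 69.0/√(2(1 − r)).

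| Assumed r | σ (pg/mL) | One-SE imbalance | Shift in contrast | Share of 58 pg/mL |
|---|---|---|---|---|
| 0.5 | 69.0 | 19.9 | 10.0 | 17% |
| 0.7 | 89.1 | 25.7 | 7.7 | 13% |
| 0.8 | 109.1 | 31.5 | 6.3 | 11% |
| 0.9 | 154.3 | 44.5 | 4.5 | 8% |

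Both tables are in BNP units on the raw scale. Section 2.5.21 allows for log transformation of NT-proBNP, so the figures are indicative.

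**The case against.** The strongest reply is that the outcome is a change score, which already uses the baseline value. In a randomised comparison it is unbiased without further adjustment, and the planned sample delivers its stated power. That stands. It limits the point to efficiency and robustness.

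A second reply is that baseline NT-proBNP is not wholly absent. Section 2.5.18 gives the panel a covariate role, the article also names mixed-effects models for longitudinal trajectories, and a fuller analysis plan may exist. In part this stands: Section 2.5.21 never says that age and sex are the only covariates. But Section 2.5.18 names no model, the mixed models are described for trajectories rather than for the primary comparison, and the article does state a covariate list, twice. The sections disagree and need reconciling.

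A third reply is that the size of the gain rests entirely on an assumed correlation. That is correct, which is why a range is shown. The direction does not depend on it: under equal variances, (1 + r)/2 is below 1 for any r below 1.

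A reader might go further and infer that the trial is underpowered, with power as low as 24%, or that the planned estimate is biased. The documents support neither. The low figures apply only if the week-16 value is modelled without baseline. Section 2.5.21 leaves that open by not naming the dependent variable, but the abstract, Section 2.2 and Section 2.5.1 all point to change. The shift from imbalance is conditional on an imbalance having occurred; it averages to zero over randomisations.

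**Conclusion.** The point holds as a should-fix. The stated models omit the baseline value of the outcome, although it is measured and although another section gives the biochemical markers a covariate role. On the protocol's own outcome the analysis is valid and meets its planned power. It forgoes about 2 power points if r is 0.9 and about 10 if r is 0.5, and it gives no protection against a baseline imbalance in the one trial that will be run.

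These sizes assume equal variances at the two visits, no explanatory value for age and sex, and the raw-scale BNP planning data standing in for NT-proBNP. The loss becomes serious only on the week-16 reading, which is a contingency and is removed by naming the dependent variable.

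**What to change.** In Section 2.5.21, state the primary model as week-16 NT-proBNP (log scale if transformed) on arm, baseline NT-proBNP on the same scale, age and sex. Carry the same covariates into the fallback models. With baseline included, the arm effect is the same whether the dependent variable is change or the week-16 value, so the outcome can still be reported as change. Use the same form, each with its own baseline value, for the continuous secondary outcomes: MLHFQ score, 6-minute walk distance, estimated 1RM and the echocardiographic measures.

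Reconcile Section 2.5.18 by saying which biochemical markers enter which model, or by removing the covariate statement.

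The cost is a sentence or two of wording and one degree of freedom per model, with no new data or visits. It should be settled before outcome data are examined, because a covariate added later could look data-driven.

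### The primary analysis scale for NT-proBNP is left to a look at the data, and the log step does not say whether levels or changes are logged

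*Protocol article*

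**What the plan says.** Section 2.5.1 of the protocol article defines the endpoint as a change: "The primary outcome of this trial will be the longitudinal change in serum N-terminal pro-brain natriuretic peptide (NT-proBNP) levels", with the interval ending when the 16-week programme ends.

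Section 2.2 sizes the trial on the raw change in a related marker. In the cited BFR trial, "a post-training reduction in brain natriuretic peptide (BNP) of 73 ± 68 pg/mL was observed in the BFR group"; the corresponding fall among controls was 15 (SD 70) pg/mL. From this "a Cohen's *d* effect size of 0.83 was calculated". The resulting requirement is that "a minimum of 24 patients per group is required to achieve a statistical power of 80% with a two-tailed alpha level of 0.05".

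Section 2.5.21 gives one analysis sequence for continuous outcomes and does not exempt the primary one:

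1. If the variable is normally distributed, ANCOVA adjusted for age and sex. Assumptions are checked by eye on histograms, probability plots and residual plots.
2. If not, the log step applies: "Continuous variables with non-normal distribution will undergo logarithmic transformation to correct distribution asymmetry".
3. As a last resort, with the method left open: "If normal distribution is not achieved following transformation, generalized linear models or robust statistical methods will be applied", again with adjustment for age and sex.

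The model statement does not name baseline NT-proBNP as a covariate. Section 2.5.18 says in general terms that the laboratory markers will serve as baseline covariates, but ties this to no model. Section 2.1 describes the trial as open-label.

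**The concern.** Two things are unclear for the single result on which the trial will be judged.

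The first is what gets logged. The outcome is called a change, it is powered as a change, and the ANCOVA adjusts for age and sex only. That points to the change score as the response. A change score can be zero or negative, and the logarithm is then undefined. The text does not say that NT-proBNP levels are logged before a change or ratio is formed.

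The second is which quantity is estimated. Raw ANCOVA gives a difference in pg/mL. A log-scale analysis of levels gives a ratio. The third step could give either, or something else, depending on the family, link or robust method chosen. The choice is made after viewing the outcome data, against no stated threshold. What is at stake is whether the primary estimand, and the power to detect an effect on it, are known before the data are seen.

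**Working it through.** **Inputs (section 2.2).** Mean reduction 73, SD 68 pg/mL (BFR); mean reduction 15, SD 70 pg/mL (control); d = 0.83; 24 per group; power 80%; two-sided alpha 0.05.

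**Step 1: reproduce the plan's sample size, to see which scale it uses.**
- Pooled SD = √[(68² + 70²)/2] = 69.0.
- Difference = 73 − 15 = 58, so d = 58/69.0 = 0.84. Dividing by the control SD gives 58/70 = 0.83, the stated value.
- A two-sample t-test with d = 0.83 needs 23.8, hence 24 per group; power at 24 is 80.4%.

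The stated 24 is reproduced. The powered quantity is a raw change in pg/mL.

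**Step 2: how often would the logarithm of the change be undefined?** Take change as week 16 minus baseline and, for illustration, assume it is normal with the planning means and SDs. Then P(change < 0) = Φ(mean reduction/SD).
- BFR: Φ(73/68) = 0.858.
- Control: Φ(15/70) = 0.585.
- Average with equal arms: (0.858 + 0.585)/2 = 0.722, or about 35 of 48 completers (24 × 0.858 + 24 × 0.585 = 34.6).

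These shares show direction only. They assume normality, which is the case in which the log step would not be triggered, and they use BNP from NYHA class I–II patients, whereas this trial measures NT-proBNP in class II–III. The documents give no figures for a skewed change. The underlying point needs no percentage: one patient without a positive change is enough for the log step to fail on a change score.

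**Step 3: does the choice of scale matter?** The documents give no log-scale SD or effect, so this was simulated under outside assumptions: log-normal levels, log SD 0.7 to 1.0, within-patient correlation 0.8, 24 per arm, true extra log reduction 0.4 to 0.6 in one arm, unadjusted t-tests, and a Shapiro test standing in for the visual check.

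| Quantity | Range over scenarios |
|---|---|
| Trials in which the raw change failed the normality test | 77% to 96% |
| Power, raw change | 27% to 85% |
| Power, log ratio | 58% to 99% |
| Trials in which the two scales disagreed on significance | 14% to 44% |
| Type I error when the test picks the scale (no true effect) | 4.7% to 4.8% |

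Under these assumptions the fallback would be the usual path and the scale would often decide the verdict, but choosing between the two scales by a formal test did not inflate the type I error. The simulation does not cover visual judgement or the open third step.

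**The case against.** The strongest reply is that the log rule is workable. It speaks of continuous variables; the measured variable is serum NT-proBNP, which is positive, and logging a skewed biomarker ordinarily means logging its levels. Section 2.5.21 also plans mixed-effects models for longitudinal data, which fit a level-based analysis. This stands in part: the rule fails only if the change is logged. But the text never says that levels are logged, and the endpoint definition, the sample size and the covariate list all point to a change score.

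Three stronger readings are tempting and are not supported.

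- **Patients would be dropped by the sign of their response.** The plan does not say this. Section 2.5.21 requires every randomised participant to be evaluated in the allocated arm, so dropping them would breach its own intention-to-treat rule.
- **The sequence inflates the type I error.** The trigger is distributional shape, not the p-value, and the only calculation available gave 4.7% to 4.8%. Inflation from discretionary judgement or the third step is not ruled out, but it is not shown.
- **Most changes are known to be negative.** That rests on a BNP proxy and on normality, and in the control arm the share is only 58%.

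It may also be said that the choice of GLM family or robust method belongs in an analysis plan that is not shown. That is fair for the detail of the third step. It does not answer the main point, because the article itself states the data-driven switch and applies it to the primary outcome.

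**Conclusion.** The point holds in this form: the protocol fixes a normality-driven sequence, judged by eye in an open-label trial, that leaves the primary estimand to be settled after the outcome data are seen. The log step is undefined for any zero or negative change if the change score is the response, and unstated if levels are meant.

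The consequence lies in the estimand, the power and possibly the verdict. Its size cannot be derived from the documents, which give no log-scale figures; the disagreement of 14% to 44% and the power ranges rest wholly on the simulation assumptions. The finding does not depend on them. It follows from the endpoint definition, the sample-size basis and the stated sequence read together.

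**What to change.** Prespecify one primary analysis: ANCOVA of ln(NT-proBNP) at week 16 on arm, with ln(baseline NT-proBNP), age and sex as covariates, reported as a ratio of geometric means with its 95% CI. Remove the normality-driven switch for the primary outcome, keep residual plots as a check only, and give the pg/mL change descriptively.

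In section 2.2, state that the sample size was derived from d = 0.83 on the raw BNP change, and that a standardised difference of that size on the log scale is an assumption, because no log-scale SD is available. The 0.83 should not be carried over as if it had been derived there.

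The cost is small: baseline and week-16 NT-proBNP are already collected, so no patients, visits or assays are added. The downside is that the effect is read as a percentage ratio rather than in pg/mL, so the powered quantity and the reported quantity differ in scale, and the text should say so. The change should be made before outcome data are examined by arm; afterwards it would no longer be prespecified.
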